**Outcomes**

Mean number of sick days in children under 48 months of age

**e.4.Study site and population**

The study will link to Stage 2 – component A – “effects of restricted use of ACTs based on RDT results: a randomised controlled trial”**.** Outcomes will be measure in this RCT and costs will be measured in 7 out of the 28 health centres involved in the trial.The health centres involved in the costing exercise will be selected using simple random sampling from those selected for the trial.

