***Secondary:***

1. What is the effect of restricting ACT to RDT positive cases of malaria on the incidence of severe anaemia?
2. What is the effect of restricting ACT to RDT positive cases of malaria on the incidence of other severe febrile diseases?
3. What is the effect of RDT on the use of antibiotics for treating febrile illness?
4. Is restricting ACT to RDT positive cases of malaria cost-effective?
5. What is the effect of RDT on the community perception of the quality of care and the treatment seeking behaviour in particular for febrile illness in young children?

**d.2. Study design**: Cluster randomised two arm trial

**Study area**: The study will be conducted in Kintampo Health Research Centre field research area in Ghana. There are 36 government health facilities in the seven districts. The catchment population of these health facilities range from 10,000 to 85,000.

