**d.4. Study groups and enrolment of study children**:

The unit of randomisation will be health centres (HC). HCs will be randomly assigned either to the RDT+ACT group (ACT offered to RDT positive cases only) or to the clinical judgement+ACT group (ACT offered to all suspected cases of malaria by clinical judgement). Households within 10km radius of the HCs will be enumerated and one hundred <24 month old children from these households will be enrolled after obtaining informed consent from caretakers in each HC. At enrolment a photoID card of study children will be given to the caretakers and they will be advised to bring the photoID card when ever they bring the study children to the health facilities for treatment. The intervention and follow up will be continued for 24 months from enrolment.

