**d.8. Sample size**:

***Effect of RDT+ACT on in the incidence of malaria***: To assess the effect of RDT+ACT on the incidence of malaria children under 48 months of age would require 30 clusters (15 per arm) and 200 PYAR per cluster on the basis of the following assumptions: (1) Incidence of malaria in the clinical judgement + ACT group would be 0.8 episode/ 1 PYAR (the rate observed in the IPTi group of <24 month old children in Navrongo, Ghana6); (2) The study would have 80% power at 95% significance level to detect a 20% difference in the incidence of malaria between the two comparison groups and this level of difference is deemed to be the non-inferiority margin of public health importance; (3) the coefficient of variation in the incidence of malaria between clusters will be 0.18

***Effect of RDT+ACT on in the incidence of severe anaemia***: Incidence of severe anaemia in the RDT + ACT group is expected to be 37/1000 PYAR (the rate observed in the 16-24 month old children who received placebo in Navrongo, Ghana6). The study would have 80% power at 95% significance level to detect a 36% reduction in the incidence of severe anaemia between the two comparison groups.

***Effect of RDT + ACT on febril children requiring referral:*** Actively following up 2000 episodes of febrile illness seen at 20 study HCs will have 85% power to detect 50% difference between the two arms assuming 1) risk of referral in the RDT + ACT group would 0.05; (2) the coefficient of variation in the risk of referral 0.1

Although mortality will be measured the study does not have adequate power to detect any difference between the groups.

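### The protocol gives two counts of randomised health centres, 30 in d.8 and 28 in e.4, and nothing reconciles them

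*Protocol*

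**What the plan says.** Protocol d.8 (Sample size) states that the primary malaria comparison "would require 30 clusters (15 per arm) and 200 PYAR per cluster". Its inputs are: "Incidence of malaria in the clinical judgement + ACT group would be 0.8 episode/ 1 PYAR"; "80% power at 95% significance level to detect a 20% difference in the incidence of malaria"; and a between-cluster coefficient of variation of 0.18. The same 20% is also called the non-inferiority margin.

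Protocol e.4 (Study site and population, cost-effectiveness component) links itself to the same randomised trial and says "costs will be measured in 7 out of the 28 health centres involved in the trial". The seven costing centres are a simple random sample of the centres selected for the trial, so 28 is given as the trial total and not as the size of a costing subset.

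Protocol d.4 makes the health centre the unit of randomisation but does not say how many there are. It does fix the size of each cluster: "one hundred <24 month old children from these households will be enrolled" per health centre, and "The intervention and follow up will be continued for 24 months from enrolment". Protocol d.2 (Study area) says "There are 36 government health facilities in the seven districts".

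**The concern.** In a cluster-randomised trial the number of clusters largely determines power. It also sets enrolment, training, test supply and budget. Here it appears twice with different values, and the section that describes randomisation (d.4) does not settle which applies. The protocol mentions no withdrawal or exclusion of centres that would turn 30 into 28, and neither figure comes from a log of superseded text.

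A team working from e.4 could randomise two centres fewer than d.8 says are needed. A team working from d.8 would have a costing section whose sampling frame is the wrong size.

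**Working it through.** **Inputs.** From d.8: control rate λ0 = 0.8 per person-year, 20% difference, 80% power, 5% significance (sidedness and direction not stated), coefficient of variation k = 0.18, y = 200 person-years per cluster. The last agrees with d.4: 100 children × 2 years = 200.

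**Formula.** Standard cluster-rate (Hayes–Bennett) sample size per arm:

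c = 1 + (zα + zβ)² × [(λ0 + λ1)/y + k²(λ0² + λ1²)] / (λ0 − λ1)²

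**The plan's figure of 15 per arm.** It can be reached from d.8's inputs in at least two ways.

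- Non-inferiority with equal true rates of 0.8, margin 0.2 × 0.8 = 0.16, one-sided 2.5%, no +1 term. Variance term: 2 × (0.8/200 + 0.0324 × 0.64) = 0.04947. At 15 per arm the standard error is √(0.04947/15) = 0.0574, and 0.16/0.0574 − 1.96 = 0.83, so power is 79.6%.
- A 20% rise (0.8 to 0.96), one-sided 5%, no +1 term: c = 14.34, rounded up to 15.

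**The figure of 14 per arm.** The same inputs, read as a two-sided 5% test for a 20% fall (0.8 to 0.64) with the +1 term:

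- (0.8 + 0.64)/200 = 0.0072
- 0.18² × (0.64 + 0.4096) = 0.0340
- sum 0.0412; divided by 0.16² = 0.0256 this is 1.610
- c = 1 + 7.849 × 1.610 = 13.63, rounded up to 14 per arm, or 28 in all.

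So both counts can be derived from d.8's inputs, and the arithmetic alone does not show which is intended.

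**Size of the trial.** 30 × 100 = 3,000 children and 30 × 200 = 6,000 person-years; 28 × 100 = 2,800 and 28 × 200 = 5,600. The difference is 200 children and 400 person-years.

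**Malaria power, 15 versus 14 per arm.**

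| Reading | 15 per arm | 14 per arm |
| --- | --- | --- |
| 20% fall, two-sided 5%, with +1 | 83.9% | 81.1% |
| Non-inferiority, margin 0.16, one-sided 2.5%, no +1 | 79.6% | 76.8% |
| Same, with +1 | 76.8% | 73.7% |
| 20% rise, one-sided 5%, no +1 | 81.5% | 79.1% |

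For the first row: √(14/1.610) − 1.96 = 0.99 gives 83.9%, and √(13/1.610) − 1.96 = 0.88 gives 81.1%.

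**Severe-anaemia power.** d.8 gives 37 per 1000 person-years and a 36% reduction, taken here as 37 to 37 × 0.64 = 23.7 per 1000. It states no coefficient of variation for this outcome, so a range is assumed (two-sided 5%, with +1):

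| Assumed coefficient of variation | 15 per arm | 14 per arm |
| --- | --- | --- |
| 0 | 81.6% | 78.7% |
| 0.1 | 79.2% | 76.2% |
| 0.18 | 74.1% | 70.9% |

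**Referral power.** d.7 and d.8 base this on 10 centres per arm (20 in all) and 2000 episodes. It is the same with 28 or 30 centres in the trial.

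**The case against.** The strongest reply is that d.8 is the section whose job is to set the size, and it does so plainly, while e.4 mentions 28 only in passing. On that view the size is stated once in the right place and miscited once, and the remedy is a one-figure edit. Much of this stands. The loss is about 3 points, and for a two-sided test of a 20% fall 28 centres still give 81.1%, above the stated 80%. It does not remove the contradiction. e.4 is current text about the same trial, d.4 is silent, and 28 is also what the usual two-sided formula yields, so it cannot be dismissed as an obvious misprint.

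Four stronger inferences are tempting but not supported:

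- *Every power figure is unsettled.* The referral figure rests on 20 centres and is unaffected.
- *The severe-anaemia and non-inferiority comparisons already lack power at 30.* For anaemia this depends on a coefficient of variation that the protocol does not give and on the +1 term: without that term, 15 per arm gives 84.2%, 81.9% and 76.9% at 0, 0.1 and 0.18. For non-inferiority it depends on sidedness, which is not stated: at one-sided 5% with the +1 term, power is 85.2% at 15 per arm and 82.9% at 14.
- *e.4 preserves one version of the calculation and d.8 another.* The arithmetic permits this, but a stale or mistyped figure is equally possible.
- *All of d.8 must be recomputed.* If 30 is kept, this mismatch requires no change to d.8.

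**Conclusion.** The inconsistency is real: 30 centres in d.8, 28 in e.4, no count in d.4 and no explanation. If 28 were randomised, the requirement stated in d.8 would be missed by two centres, 200 children and 400 person-years, and malaria and severe-anaemia power would fall by about 2.5 to 3 points. The malaria figures rest on d.8's inputs plus an assumed direction, sidedness and use of the +1 term. The anaemia figures rest in addition on an assumed coefficient of variation of 0 to 0.18. The loss from 30 to 28 is much the same under all these readings, whereas the absolute power is not.

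This is a correction that should be made before randomisation because it concerns the basic size of the trial. It is not evidence that the trial is underpowered, and the protocol does not show which number the team intends.

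**What to change.** State one number of randomised health centres, the same in d.4, d.8 and e.4.

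- If it is the 30 that d.8 requires, which the 36 available facilities allow, change e.4 to 7 out of the 30 and add the count to d.4. d.8 stays as it is on this point. The cost is wording only, provided 30 was always the plan. If 28 was the working number, moving to 30 adds two centres, 200 children and 400 person-years.
- If 28 is the number actually planned, change d.8 to 28 clusters (14 per arm) and restate the malaria and severe-anaemia power for 14 per arm, giving the sidedness, the direction of the 20% and the coefficient of variation used for anaemia. The cost is a recalculated paragraph.

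The referral statement needs no change in either case.

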**d.7. Measuring outcomes**:

***Incidence of malaria:***

Passive surveillance: All study children presenting with a history of fever to the study HCs will be identified using photoID cards and assessed with a morbidity questionnaire and a blood sample (blood slide and filter paper) will be collected to assess malaria parasite. Since the decision to offer an antimalarial drug will be based on RDT results or clinical judgment the blood slides will have limited use for treatment decision making. However, the blood slides will be at Kintampo Health Research Centre and the results will be reported to the health centres.

Active surveillance: Study children will be visited once a month at home and a morbidity questionnaire and blood samples (blood slide and filter paper) will be collected to assess malaria parasite if a child has a history of fever in the past 48 hours. Those who have a positive blood slide will be treated with ACT.

Both passive and active surveillance of malaria will be continued for 24 months from enrolment.

***Incidence of severe anaemia***:. All study children attending study HCs will be clinically assessed using a morbidity questionnaire and the Hb will be tested using a haemacue machine if anaemia is suspected by clinical examination. Children with Hb <11 gms/dl will be given appropriate treatment according to the national treatment protocol.

***Incidence of severe febrile illness and mean number of sick days:*** These outcomes will be measured in 100 episodes of febrile illness (50 in the wet and 50 in the dry season) in 10 randomly selected study HCs per arm. These children will be actively followed up on day 1,2,3 and 7 post treatment to assess the progress of their illness. If the illness has resolved by day 7, the number days the child was ill will be collected from the caretaker’s report. If the illness has not resolve by day 7 the child will be referred to the hospital and the number of days of illness will be collected from hospital discharge summary. The mean number of days of illness and the proportion of children requiring reference will be compared between the two groups.

***Use of antibiotics:*** The use of antibiotics will be monitored through the morbidity questionnaire completed during each visit to the study PHCs by study children.

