**e.6.Data analysis**

Both cost effectiveness ratios and an incremental cost and consequences analysis of RDT based versus clinical judgement based ACT will be assessed. Modelling of the outcomes to Disability Adjusted Life Years (DALYs) will be undertaken as per ACT Consortium economic evaluation guidance.

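### The 7 costed health centres are drawn without regard to arm, so about two draws in five leave one arm of the cost comparison with two or fewer centres

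*Protocol*

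**What the plan says.** Section e.4 sets the size of the costing sample, "costs will be measured in 7 out of the 28 health centres involved in the trial", and then the method: "The health centres involved in the costing exercise will be selected using simple random sampling from those selected for the trial". It gives no stratification by arm and no minimum number per arm.

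The rest of the protocol makes arm matter here. Section d.2 describes a "Cluster randomised two arm trial", and d.4 states "The unit of randomisation will be health centres (HC"). Section e.1 makes the cost-effectiveness of one strategy against the other the primary question of component B. Section e.3 lists a treatment cost for each strategy, and e.6 says that "an incremental cost and consequences analysis of RDT based versus clinical judgement based ACT will be assessed".

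Elsewhere the protocol does sample by arm. For the follow-up of febrile episodes, d.7 takes them "in 10 randomly selected study HCs per arm".

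The number of centres also differs between sections: e.4 works from 28, while the primary sample size in d.8 "would require 30 clusters (15 per arm) and 200 PYAR per cluster".

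**The concern.** An incremental cost needs cost data from both arms. Because the centre is the unit of randomisation, a costed centre cannot contribute to both. A simple random sample from the pooled list leaves the split between arms to chance, and with only seven centres chance matters. The smaller arm may have two centres, one or none.

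At stake is the precision of the cost side of component B. In the worst draws, its feasibility is at stake too. The protocol names the selection rule, so this is not a detail left to an analysis plan. An analysis plan could not repair it anyway once costs had been collected in a badly split set of centres.

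**Working it through.** The protocol gives no power, precision or per-arm count for the costing sample, so there is no stated figure to reproduce. The check is the exact distribution of the split that the stated rule produces.

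**Inputs**
- Centres drawn: 7 (e.4).
- Frame: 28 centres (e.4); 30 as the alternative (d.8).
- Allocation: d.8 gives 15 per arm for 30 centres. Section e.4 gives no split for its 28, so 14 per arm is an assumption.

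**Formula.** The number k of costed centres in a named arm is hypergeometric: P(k) = C(14,k) × C(14,7−k) / C(28,7), with C(28,7) = 1,184,040.

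| Smaller arm | Draws for a named arm | Either arm (doubled) | Probability |
| --- | --- | --- | --- |
| 0 | 1 × 3,432 = 3,432 | 6,864 | 0.58% |
| 1 | 14 × 3,003 = 42,042 | 84,084 | 7.1% |
| 2 | 91 × 2,002 = 182,182 | 364,364 | 30.8% |
| 3 | 364 × 1,001 = 364,364 | 728,728 | 61.5% |

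The doubled counts add up to 1,184,040, as they should. Cumulatively:
- at most one centre: (6,864 + 84,084) / 1,184,040 = 7.7%
- two or fewer: (6,864 + 84,084 + 364,364) / 1,184,040 = 38.5%

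**Sensitivity to the assumed split**

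| Centres per arm | Two or fewer | At most one | None |
| --- | --- | --- | --- |
| 14 + 14 | 38.5% | 7.7% | 0.58% |
| 15 + 15 | 39.0% | 8.0% | 0.63% |
| 13 + 15 | 39.6% | 8.4% | 0.69% |
| 12 + 16 | 42.8% | 10.4% | 1.0% |

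**Effect on precision.** With equal between-centre variance in the arms, the standard error of the difference is proportional to √(1/n₁ + 1/n₂):
- 3:4 gives √(1/3 + 1/4) = 0.764
- 2:5 gives √(1/2 + 1/5) = 0.837, a ratio of 1.10
- 1:6 gives √(1/1 + 1/6) = 1.080, a ratio of 1.41

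Averaged over the draws in which both arms are represented: (0.615 × 1 + 0.308 × 1.095 + 0.071 × 1.414) / 0.994 = 1.06. The mean penalty is therefore about 6%.

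**After stratifying by arm (3 and 4).** The probabilities of two or fewer, at most one and none all become zero.

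**The case against.** The strongest reply is that the practical loss is modest. Outright failure needs an arm with no costed centre, which happens in about 0.6% of draws. Most of the 38% are 2:5 splits, which cost about 10% in standard error, and the average penalty is about 6%. The main weakness is having seven centres in all, and a 3:4 split does not cure that. This stands, and it limits the size of the point.

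A reader might infer that any arm with two or fewer centres has no usable between-centre variance. That is not so. Two centres give a poor estimate, but they give one, and a variance pooled over arms is still available. Only with a single centre can the arm's own variance not be estimated.

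A reader might also infer that arm becomes confounded with centre size, since d.2 gives catchments of 10,000 to 85,000. That range is given with the 36 government facilities in the area, not for the trial centres. Stratifying by arm would not balance size in any case. Chance imbalance is possible under either rule, but the protocol does not demonstrate confounding.

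Nor does it follow that the whole incremental cost rests on the seven centres. Section e.5 includes trial expenditure that may come from project accounts, and d.7 records antibiotic use at every visit by study children. But e.4 says without qualification that costs are measured in the seven, so the protocol does not settle how much would come from elsewhere.

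Finally, cost-effectiveness is a secondary question of the trial (d.1), and the primary malaria outcome is untouched. That bears on priority. It does not justify leaving the split to chance, and the protocol states no advantage of the pooled draw.

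**Conclusion.** The point holds in graded form. The rule in e.4 does not control how the seven costed centres fall between arms, although component B's primary question needs both. With 14 centres per arm, 38% of draws leave an arm with two or fewer costed centres (31% with exactly two), 7.7% with at most one and 0.6% with none. The consequences run from a mild loss of precision, through an arm with no variance estimate of its own, to no comparison at all in rare draws. To say that the cost comparison will probably fail would go beyond these figures.

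The probabilities rest on the assumed 14 per arm, and change little for 15 + 15 or for mildly unequal splits. The standard-error ratios rest on equal between-centre variance in the two arms. The 28 against 30 mismatch is a separate inconsistency and does not drive the conclusion. It matters here only because the frame must be known before the draw.

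**What to change.** In e.4, replace the pooled draw by random selection within arm after allocation: three centres from one arm and four from the other, with the arm that receives four chosen at random or fixed in advance. This follows the by-arm selection already used in d.7. In the same edit, reconcile the number of trial centres between e.4 (28) and d.8 (30), so that the frame is the actual list of randomised centres.

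The change takes a sentence or two, keeps random selection and needs no additional centre. It removes the arm imbalance. It does not make seven centres a large sample or assure balance on centre size, and the report of the cost analysis should say so. There is no need to restrict the draw to the centres with active follow-up on days 1, 2, 3 and 7, because that contact might itself alter the costs observed.

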**e.5.Costing study procedures**

Both financial and economic costs will be measured. The financial costs will include all direct expenditure on the trial including salaries, this will include stage 2 components only, the costs of stage 1 components will not be included. The economic costs will include financial costs plus any opportunity costs including travel time to health facilities. Capital costs will include any equipment purchased for the trial that will be used for more than one year. Development and set up costs involving training of health centre staff will be included as capital costs as their impact is expected to be for more than one year. A costing framework will be used to categorise all costs and their categories and will include 1) design development, 2) project set-up, and 3) project implementation. Findings from the delivery systems determinants study, Stage 1 component B will be used to identify cost categories.

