**PROPOSED STARTING DATE: 1 January 2009**

**DURATION (MONTHS): 48 months**

**TOTAL BUDGET REQUESTED: US$ 1,473,510**

**TOTAL BUDGET SPEND IN NORTHERN INSTITUTIONS* US$**

**INSTITUTION WHERE GRANT TO BE HELD: London School of Hygiene & Tropical Medicine**

**SITE(S) OF RESEARCH (COUNTRIES, LOCATIONS, INSTITUTIONS):**

Kintampo Health Research Centre’s field research area in Ghana

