**e.2. Study perspective**

The societal perspective will be taken and therefore will include costs to all those involved in the project including the children with fever and their carers. The provider perspective will be taken in assessing the cost implications for a DHMT of introducing RDTs into their health centres.

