**e.3. Primary costs and outcomes**

**Costs**

Cost of treatment of febrile children with ACT based on positive RDT tests

Cost of treatment of febrile children with ACT based on clinical judgement

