**Secondary costs and outcomes**

**Costs**

Cost of treatment of febrile children under 48 months (ACTs + antibiotics + other treatments) in those tested with an RDT

Cost of treatment of febrile children under 48 months (ACTs + antibiotics + other treatments) based on clinical judgement alone

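### The costing rule in e.5 does not separate research-only expenditure from the cost of delivering each strategy, and the primary cost in e.3 appears to leave out antibiotics and other treatments

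*Protocol*

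**What the plan says.** **Which expenditure counts (e.5).** The rule is that "The financial costs will include all direct expenditure on the trial including salaries". One limit follows: "this will include stage 2 components only, the costs of stage 1 components will not be included". On equipment: "Capital costs will include any equipment purchased for the trial that will be used for more than one year". Economic costs are these financial costs with opportunity costs added. The costing framework "will include 1) design development, 2) project set-up, and 3) project implementation".

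**Which treatment costs count (e.3).** In the RDT arm the primary cost is "Cost of treatment of febrile children with ACT based on positive RDT tests", with a matching line for ACT given on clinical judgement. The secondary cost in the RDT arm covers "ACTs + antibiotics + other treatments) in those tested with an RDT", again with a matching line for the other arm.

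**Whose costs count (e.2).** The main analysis takes the societal perspective. For the district question, "The provider perspective will be taken in assessing the cost implications for a DHMT of introducing RDTs into their health centres".

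**What is reported (e.6).** Cost-effectiveness ratios are planned together with an incremental cost and consequences analysis.

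**The concern.** Stage 2 contains work that exists because this is a trial. Households are enumerated and children given photo cards (d.4). Blood slides and filter papers are collected, and children are visited at home every month for surveillance (d.7). A district adopting either strategy would not buy this package, yet the rule in e.5 counts it.

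The primary cost has the opposite problem: it looks too narrow. Staff in the RDT arm are trained to investigate RDT-negative children for other infections (d.6), and antibiotic use is a secondary outcome (d.3). Non-ACT care is therefore one of the things the intervention could change, but the headline cost does not name it.

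At stake are the main answer of component B and the secondary question on what RDT-based treatment would cost a DHMT. The trial's primary endpoint is not affected.

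**Working it through.** The protocol states no unit cost, cost per child or cost-effectiveness ratio, so there is no figure to reproduce. The check compares the sections and uses small illustrations. Every unit cost and share below is an assumption, chosen only to show how the rules behave.

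**1. Does any section remove research-only cost?**
- e.5 excludes stage 1 and nothing else.
- The three framework categories divide cost by project phase, not by research versus delivery. Surveillance visits and RDT supplies would both fall under implementation.
- Economic cost is built on financial cost, so whatever enters the first enters the second.
- The DHMT question has its own perspective in e.2 but no costing rule of its own. The only rule on the page is e.5.

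**2. What does a research cost R per child do?** Let C be the delivery cost per child and E the effect per child.
- Average ratio in an arm: (C + R)/E. It rises with R.
- Increment: (C_RDT + R_RDT) − (C_clin + R_clin) = (C_RDT − C_clin) + (R_RDT − R_clin).

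Assume C_RDT = 12, C_clin = 10 and R = 100 in both arms:

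| | R = 0 | R = 100 |
| --- | --- | --- |
| RDT arm | 12 | 112 |
| Clinical-judgement arm | 10 | 110 |
| Increment | 2 | 2 |
| Ratio of average costs | 12/10 = 1.20 | 112/110 = 1.018 |

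The arm costs, and so the average ratios, rise by factors of 112/12 = 9.3 and 110/10 = 11. The increment stays at 2. If R differed between arms by 2, which is 2/100 = 2% of R, the increment would become 0 or 4. Cancellation therefore depends on near-equal research cost per child. No section ensures this: e.5 gives no rule for allocating expenditure to arms, and e.4 draws 7 centres by simple random sampling, an odd number that cannot divide evenly between two arms.

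**3. What does the primary cost contain?** The primary lines name ACT only. The secondary lines name ACT, antibiotics and other treatments, and in the RDT arm they cover everyone tested rather than those who tested positive. If the primary lines already held all this, the secondary lines would largely repeat them. The natural reading is that the primary cost is ACT only. Whether it includes the test itself is not stated.

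**4. What could the narrower cost do to the increment?** Let n be the RDT-negative share and d the RDT-minus-clinical difference in other-treatment cost per febrile child. Assume an ACT costs 1 and a test 0.7, every febrile child in the clinical arm receives ACT, and n is 0.3 to 0.7.
- ACT only: (1 − n) − 1 = −n, giving −0.70 to −0.30.
- Adding the test: 0.7 − n, giving 0.00 to +0.40.
- Adding other treatments: 0.7 − n + d. In the extreme case where only RDT-negative children in the RDT arm receive them, at a cost a of 0.5 to 2, d = n × a. The result runs from 0.7 − 0.7 + 0.7 × 0.5 = +0.35 to 0.7 − 0.7 + 0.7 × 2 = +1.40.

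With these inputs, adding the test removes the apparent saving, and other treatments then widen the gap. If d = 0, omitting other treatments does no harm to the increment. If d is negative, omitting them favours clinical judgement instead.

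**The case against.** A health economist could answer as follows.

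- **Listing is not charging.** e.5 says what financial costs include, not how they are assigned to arms or ratios. The framework would let design development be set aside. This stands, and a reader who infers that every dollar of the trial will be charged to the strategies goes further than the text. But the framework does not separate research from delivery within implementation, and e.5 states an inclusive rule rather than leaving the matter open.
- **Common costs cancel.** e.6 plans an incremental analysis, where equal research costs drop out. This also stands, so the text does not support the inference that the cost-effectiveness result must be wrong. The planned ratios remain exposed if they are calculated per arm, as their listing beside the incremental analysis suggests.
- **The DHMT question has its own perspective.** It does, and no section says the e.5 total will answer it. The inflation is conditional on that total being used.
- **The primary lines may only name the two strategies.** No exclusion of antibiotics is written, so the omission is an inference from contrast. The fuller cost is planned in both arms, so no information is lost. What remains is which cost leads.
- **The direction of bias is unknown.** The research question on antibiotics is open, and d.6 also gives clinical-judgement staff refresher training on other infections with similar signs. A reader might infer that the primary cost is biased towards RDT; the documents support only that it may be.

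**Conclusion.** The point holds as a defect in the costing rules, not as a demonstrated error in a result.

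- Applied as written, e.5 inflates each arm's average cost-effectiveness ratio, and the DHMT cost if that is built on the same total. The increment is safe only if research cost per child is equal between arms.
- On the natural reading of e.3, the headline cost comparison omits non-ACT treatment and is narrower than the societal perspective in e.2. It may favour the RDT strategy, depending on antibiotic and other-treatment use that the protocol does not give.

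No dollar size can be attached. A reader might divide the budget ("TOTAL BUDGET REQUESTED: US$ 1,473,510") by the planned 30 × 200 = 6,000 person-years and take the resulting US$246 as the loading. That total is for the whole project, including the stage 1 work that e.5 excludes, and the protocol gives no research share of it. The illustrations show how the rules behave and do not estimate an effect.

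**What to change.** **In e.5:** tag each cost line as research or delivery, and exclude research-only lines from both the strategy costs and the DHMT cost. Write the classification down before results are known, because some lines need judgement. Home visits, for example, are surveillance but also lead to treatment of slide-positive children. State that the DHMT cost is built from the delivery lines only.

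**In e.3:** make the already planned all-treatment cost per febrile child the primary cost, covering the test, ACT, antibiotics and other treatments for RDT-positive and RDT-negative children alike. Keep the ACT-only cost as secondary.

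**Cost:** rewording two sections and some extra work in classifying expenditure. No new data are needed, since antibiotic use is already recorded at each health-centre visit (d.7) and the all-treatment cost is already planned.
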